#### Full trial

A further 302 participants (332 participants in total) will be recruited over seven sites: Newcastle, Sunderland, Nottingham, Brighton, Glasgow, Manchester and Birmingham.

### Intervention

The active intervention is a 16-week (4-month) course of a 30 mg twice daily dose of the PPI lansoprazole.

### Control

Participants in the control arm will receive a 16-week (4-month) course of twice-daily matched placebo capsule.

### Study compliance and withdrawal

Where feasible, visit windows of ±14 days should ensure visit attendance; non-attendance for study visits will prompt follow-up by telephone.

Compliance with study medication will be assessed by checking and recording the remaining number of capsules at the end of the treatment period by a member of the study team. Study drug accountability will be assessed and documented by local pharmacy before being destroyed.

#### Withdrawal of participants

Study drug must be discontinued if:the participant decides that he/she no longer wishes to continue, orcessation of study drug is recommended by the PI.

Participants have the right to withdraw from the study at any time for any reason, and without giving a reason. The PI also has the right to withdraw participants from the study drug in the event of intervening pregnancy, inter-current illness, adverse events, serious adverse events, suspected unexpected serious adverse reactions, protocol violations, cure, administrative reasons or other reasons. It is understood by all concerned that an excessive rate of withdrawals can render the study uninterpretable; therefore, unnecessary withdrawal of participants should be avoided. Should a participant decide to withdraw from the study, all efforts will be made to report the reason for withdrawal as thoroughly as possible. Should a participant withdraw from the study drug only, efforts will be made to continue to obtain follow-up data, with his/her permission.

Participants who wish to withdraw from study medication will be asked to confirm whether they are still willing to provide the following:Study-specific data at follow-up visits at 4 and 12 months.‘End of study data’ as per the visit at 12 months, at the point of withdrawal.If participants agree to either of the above, they will be asked to complete a confirmation of withdrawal form to document their decision.

Participants who withdraw from the study will not be replaced.

### Statistical analysis

The primary outcome measure of change in RSI score after 4 months will be analysed using analysis of covariance (ANCOVA) methods in order to compare the change in RSI between the trial arms while adjusting for potential confounders including the stratification variables used at randomisation of site and baseline severity (as defined by the binary RSI cutoff value) as covariates in the analysis. We will also consider adjusting for gender, age, body mass index, baseline laryngeal appearance scores by the RFS and categories of symptoms. Not all of these covariates mentioned will necessarily be included in the final model but will be considered during the model selection process.

Should data be found to be non-normally distributed the use of transformations or non-parametric approaches will be considered, although as ANCOVA is generally robust to departures from normality the aforementioned approach is likely to be followed. More basic exploratory analyses may be undertaken using the two-sample *t* test or non-parametric alternatives.

The analysis of secondary outcomes will follow a broadly similar strategy when considering questionnaire scores or the change in questionnaire scores. The proportion with follow-up RSI scores within versus out with the published normal range will be analysed using a logistic regression approach, once more adjusting for the covariates as already described for the primary outcome.

The primary analysis will be carried out on an intention-to-treat basis; other analysis groups, such as per protocol, may be considered subsequently. Outcome data will be analysed at the end of the study. There are no planned interim analyses and a full statistical analysis plan will be developed prior to the start of analysis. Safety data will not be subject to statistical analysis. Data with missing observations due to loss to follow-up will be examined to determine both its extent and whether it is missing at random or is informative. If data are missing to a sufficient extent, the use of appropriate multiple imputation techniques will be considered.

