#### Outcomes

The RSI remains the ‘area standard’, and despite well-rehearsed limitations [21] is therefore our chosen primary outcome in the present proposal. Some reported studies have a baseline RSI only just above the normal level, others considerably higher. A Korean observational study of 455 patients reported that the mean RSI score fell from 15 at baseline to <6 after 12 weeks of the PPI rabeprazole [22]. Baseline RSI scores in a much smaller but comparative study of 62 patients treated with esomeprazole were considerably higher (>20) [23], whereas baseline scores in a rabeprazole randomised controlled trial were around 14 [13]. Two trials showed a benefit from a 3-month trial of acid suppression – but Lam et al. [13] continued follow up for a further 6 weeks, when the effect disappeared, while Reichel et al.’s [24] final measurement point was the end of therapy.

Throat symptoms impact on general health status measures [25, 26]. A tool specifically designed to assess throat symptom patients is the LPR-HRQL tool [27, 28], which has also been validated in a Swedish population [29]. Its 43 items are grouped into four domains and an overall impact category, and the tool appears responsive to change [30].

The TOPPITS primary outcome is the change in RSI at 4 months in the treatment and placebo groups in an intention-to-treat analysis. The nine-item RSI total score (0–45) allows comparison with previous studies. We plan, however, to report also the RSI score omitting the heartburn item (0–40), which we and others note can skew the results in favour of PPIs in past small trials. Our proposed analysis will also address the issue of severity variation, through our stratification variables of site and baseline severity.

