### Sample size calculation

The primary outcome measure is the change in the RSI score from baseline to the 4-month assessment. We believe a clinical effect of 0.4 (equivalent to a difference in change of RSI of 3.1 given a standard deviation of 7.7 [34]) is a reasonable target based on prior LPR therapy studies. Further, an effect size of 0.4 is of smaller magnitude than the effect of phonomicrosurgery or speech therapy. A similar effect size is predicted from the more limited amount of published data available on the LPR-HRQL. For a two-sample *t* test, 90 % power and at the 0.05 significance level, allowing for 20 % loss to follow-up, we require 332 patients (166 in each arm of the study) to give 266 (133 in each arm) completing the study. Two other recent reports of LPR drug studies show lower than 7 % dropout rates. Our NHS experience, however, suggests that this is overly optimistic for a trial of this kind. Because the literature is well populated with underpowered low-impact studies, we prefer to err on the side of caution and hence our sample allows for a 20 % attrition rate.

Participant recruitment into the pilot phase will be for a total of 6 months. We estimate that each site will be able to recruit 10 participants per 3-month block once the study is established. However, as research studies usually take some time to become embedded into practice, we have calculated recruitment across the whole trial based on lower recruitment in three sites during the first 6 months. Our predicted recruitment allows for each of the three sites to recruit 30 % (three participants) in the first 3 months, and 70 % (seven participants) in the second 3 months. We aim for those three sites to be recruiting to full target (10 participants per 3 months) thereafter in the main trial, with equivalent run-in for the remaining three sites.

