### Study design and duration

This is a multi-centre, phase III, randomised, double-blind, placebo-controlled trial, with internal feasibility pilot, carried out in secondary care. Patients will be randomised into two parallel streams on a 1:1 ratio stratified by site and baseline severity (two groups, on the basis of the RSI score). Following successful demonstration of recruitment in three sites in the internal pilot, a definitive trial will be conducted over 30 months. Patients with persistent throat symptoms will be identified and recruited from ENT clinics.

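### The only baseline RSI term named for the primary ANCOVA is the two-level severity group; adding the numeric baseline score would recover precision at no cost.

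*Protocol article*

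**What the plan says.** The primary outcome is the change in RSI total from baseline to 4 months (Outcomes; Sample size calculation). The Statistical analysis section compares this change between arms by ANCOVA, with "site and baseline severity (as defined by the binary RSI cutoff value) as covariates in the analysis". It then lists covariates that may be added during model selection: gender, age, body mass index, the baseline Reflux Finding Score and symptom categories. Baseline RSI as a number is not on that list.

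Two other sections agree. Outcomes says: "Our proposed analysis will also address the issue of severity variation, through our stratification variables of site and baseline severity". Study design and duration describes patients "randomised into two parallel streams on a 1:1 ratio", stratified by site and by two RSI severity groups. The cutoff value and the expected split between the groups are not given.

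Outcomes gives the RSI total a range of 0 to 45. The Statistical analysis section says that secondary questionnaire scores will follow a broadly similar approach, that the logistic model for RSI within the normal range will use the same covariates, and that a full analysis plan will be written before analysis starts.

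**The concern.** A change score contains its own baseline with a negative sign, so patients who start higher generally have more room to fall. The baseline score is usually the strongest single predictor of change. Here it enters only as high or low. Two patients in the same group may start many points apart, and the model treats them as alike. The variation between them goes into the residual, and the standard error of the treatment effect is larger than it needs to be.

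The article is not merely silent. It names the form of the baseline term and lists five optional covariates without the numeric baseline. An analysis plan that follows the article would carry the two-level term forward. What is at stake is the width of the confidence interval for the primary comparison and, if the same model is copied, for the secondary scores.

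**Working it through.** **Step 1. The plan's own sample size.** Inputs from Sample size calculation: "90 % power and at the 0.05 significance level"; a standardised effect of 0.4, "equivalent to a difference in change of RSI of 3.1 given a standard deviation of 7.7" (3.1/7.7 = 0.403); "allowing for 20 % loss to follow-up". The significance level is taken as two-sided. The exact two-sample t test with effect 0.4 needs 133 per arm, or 266 in all (power 0.901). Then 266/0.80 = 332.5, against the stated result: "we require 332 patients (166 in each arm of the study) to give 266 (133 in each arm) completing the study". The figure reproduces up to rounding. It uses no covariate adjustment.

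**Step 2. Residual variance under each model.** Scale the baseline SD to 1. Let the follow-up SD be k and the baseline to 4-month correlation r. Let g be the squared correlation between the binary group and the numeric baseline. Site is left out, since it is in both models.

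- Variance of change: V = k² + 1 − 2rk
- Covariance of change with baseline: c = rk − 1
- Residual variance with the binary group: Vb = V − g·c²
- Residual variance with the numeric baseline: Vn = V − c²
- Equivalent loss of completers: 266 × (1 − Vn/Vb)
- Standard error ratio: √(Vb/Vn)

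For a normal baseline split at the median, g = 2/π = 0.637. The article gives none of r, k, g or the shape of the baseline distribution, so all are assumed.

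**Step 3. Equal SDs (k = 1), median split.** Here Vb = 2(1 − r) − 0.637(1 − r)² and Vn = 1 − r².

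| r | Vb | Vn | SE ratio | Loss out of 266 |
|---|---|---|---|---|
| 0.3 | 1.088 | 0.910 | 1.093 | 43.5 |
| 0.5 | 0.841 | 0.750 | 1.059 | 28.7 |
| 0.7 | 0.543 | 0.510 | 1.032 | 16.0 |

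**Step 4. How far this depends on the assumptions.** Losses are for r = 0.3, 0.5 and 0.7 in turn.

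| Assumption changed | Loss out of 266 |
|---|---|
| Follow-up SD 0.8 times baseline | 70.5, 57.0, 47.2 |
| Follow-up SD 1.2 times baseline | 27.1, 13.6, 3.3 |
| Follow-up SD 1.4 times baseline | 17.1, 5.8, 0.0 |
| 70/30 split (g = 0.576), equal SDs | 49.5, 33.0, 18.5 |
| 80/20 split (g = 0.490), equal SDs | 57.3, 38.7, 22.0 |

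Normality matters little. Truncating the baseline from below, at points from 1 SD under the mean up to the mean, moves g only between 0.616 and 0.654. The equal-SD loss then lies between 41.8 and 45.6 at r = 0.3 and between 15.3 and 16.9 at r = 0.7. The SD ratio matters most.

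**Step 5. Power.** Read 7.7 as the SD of change, with a difference of 3.1, 133 per arm, equal SDs and a median split. Unadjusted power is 0.907 (normal approximation). The residual SD is 7.7 × √(Vb/V) or 7.7 × √(Vn/V).

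| r | Residual SD, binary | Residual SD, numeric | Power, binary | Power, numeric |
|---|---|---|---|---|
| 0.3 | 6.79 | 6.21 | 0.961 | 0.983 |
| 0.5 | 7.06 | 6.67 | 0.947 | 0.966 |
| 0.7 | 7.32 | 7.10 | 0.932 | 0.945 |

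The numeric term adds between 0.013 (0.945 − 0.932) and 0.022 (0.983 − 0.961) to power that already exceeds 0.90.

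**The case against.** Three objections have force.

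*The list of covariates is open.* The article introduces the stratification variables as examples of the adjustment, leaves further terms to model selection, and promises a full analysis plan. A reader might infer that numeric baseline RSI is ruled out. The text does not say so. What stands is narrower: the article specifies the binary form, names no numeric term, and repeats the approach under Outcomes.

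*The trial is not underpowered by this choice.* A reader might infer that some 16 to 44 patients are lost from the planned power. That does not follow. The sample size comes from an unadjusted comparison, so the binary adjustment is itself a gain on the plan, and the numeric term would be a further gain. The size of that further gain is also uncertain. Entry requires at least 10 points on the non-heartburn items, which narrows the baseline spread. A follow-up SD above the baseline SD is therefore plausible, and the difference could then be small. This objection stands in full.

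*There is no bias.* A reader might infer that chance imbalance in baseline RSI within the severity groups distorts the result. Under equal SDs and r = 0.5, each point of imbalance would indeed shift the comparison of change by 0.5 points. But allocation is randomised, so such imbalance is chance variation that the standard error already reflects. It is the same loss of precision seen from another side, not a second defect.

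**Conclusion.** The point holds as a matter of efficiency. The article fixes the baseline RSI term in a form that discards information the trial already holds. The direction is secure: under the linear model used here, the numeric baseline gives an equal or smaller residual variance whatever the correlation, SD ratio or cutoff.

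The size is illustrative only. With equal SDs, a normal baseline, a median split and r from 0.3 to 0.7, the standard error is about 9% down to 3% larger than it need be, equivalent to about 44 down to 16 of 266 completers. With follow-up SDs of 0.8 to 1.4 times baseline, the equivalent runs from about 71 to 0. No single figure in that range can be taken from the article.

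The validity of the primary comparison and the planned 90% power are not in question. The figures apply to linear models of scores. They are not claimed for the logistic model of RSI within the normal range, where adding a prognostic covariate also changes the odds ratio being estimated. The change is worth making because it is free, not because the planned analysis would fail.

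**What to change.** In the analysis plan, keep site and the binary severity group in the primary ANCOVA, since both were used in randomisation, and add baseline RSI total as a prespecified continuous covariate that is not subject to model selection. For each secondary questionnaire score analysed in the same way, add that score's own continuous baseline. The article's wording on the binary cutoff correctly describes the stratification factor and can stay.

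The cost is about one line of text and one degree of freedom per model. For the primary analysis no new data are needed, because the change score cannot be computed without baseline RSI; the same is true of any secondary score analysed as a change. It should be settled before outcome data are examined by arm. The article plans no interim analysis and analyses outcomes at the end of the study.

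### The primary ANCOVA's covariates are left to an unspecified model selection step and its scale may follow the observed distribution, so the 5% level and the 3.1-point RSI comparison are not guaranteed

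*Protocol article*

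**What the plan says.** The Sample size calculation section of the protocol article defines the endpoint: "The primary outcome measure is the change in the RSI score from baseline to the 4-month assessment". The trial is sized for "a clinical effect of 0.4 (equivalent to a difference in change of RSI of 3.1 given a standard deviation of 7.7", with "90 % power and at the 0.05 significance level, allowing for 20 % loss to follow-up". Under Study design and duration, patients are "randomised into two parallel streams on a 1:1 ratio stratified by site and baseline severity".

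The Statistical analysis section chooses ANCOVA, adjusted for covariates that include site and the binary severity group. It then lists gender, age, BMI, baseline RFS and symptom categories as further candidates and adds: "Not all of these covariates mentioned will necessarily be included in the final model but will be considered during the model selection process". On scale it says: "Should data be found to be non-normally distributed the use of transformations or non-parametric approaches will be considered". The same sentence goes on to say that ANCOVA copes well with non-normality and will probably be kept. The section also promises a full SAP before analysis starts, plans no interim analyses, and places outcome analysis at the end of the study.

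**The concern.** The article does more than leave the covariate list open. It describes how the primary model will be reached, namely by considering candidates and keeping some of them. It does not give a criterion, an order, or a condition that the analyst work blind to allocation or to the treatment estimate. It promises a SAP but does not say that the SAP will remove the selection step, so a SAP faithful to this text could carry the step forward.

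Two things are at stake.

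- **Error rate.** The 0.05 level belongs to one test fixed in advance. If several models are fitted and the choice among them can respond to the treatment result, that level no longer applies.
- **Estimand.** The trial is powered on a difference in RSI points. A rank analysis does not estimate that difference. A log cannot be applied directly to a change score that takes negative values.

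The setting makes a benign selection harder to demonstrate afterwards. Under Objectives, age, gender, BMI and RFS are also to be studied as possible determinants of treatment response, so their relation to the treatment effect will be examined in the same data.

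**Working it through.** **1. The plan's own figure.** Inputs are from Sample size calculation: standardised effect 0.4 (3.1/7.7 = 0.403), 90% power, level 0.05 (taken as two-sided), 20% loss.

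- Normal approximation: n per arm = 2(1.960 + 1.2816)²/0.4² = 2 × 10.507/0.16 = 131.3, so 132.
- Noncentral t: 133 per arm, power 0.901.
- Loss: 133/0.8 = 166.25, stated as 166 per arm.

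This agrees with "we require 332 patients (166 in each arm of the study) to give 266 (133 in each arm) completing the study". The number is sound for one pre-fixed comparison on the RSI scale.

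**2. Number of candidate models.** Five optional covariates, each in or out, give 2⁵ = 32 models with site and severity kept throughout.

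**3. Type I error by selection rule.** Null simulation with 266 completers, seven sites, binary severity, SD 7.7 and 4,000 trials per setting. The Monte Carlo standard error at 5% is √(0.05 × 0.95/4000) = 0.34 percentage points. The article does not say how prognostic the optional covariates are, so their joint share of variance is an assumption, shown as a range. Baseline RSI was also assumed: mean 21, SD 7, split at 20, explaining a further 10% or so of variance.

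| Rule | 5% | 20% | 40% |
|---|---|---|---|
| Fixed: treatment, site, severity | 5.0% | 4.6% | 5.6% |
| Lowest AIC | 5.3% | 4.8% | 5.2% |
| Keep covariates with p < 0.10 | 5.3% | 4.9% | 5.2% |
| Most favourable of the 32 models | 8.2% | 11.6% | 18.1% |

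A second simulation, with 1,500 trials per setting and assumed shares of 5, 15 and 25%, gave 9.1, 11.9 and 13.6% for the last rule and 5.1-5.8% for single fixed models. There the median range of the treatment estimate across the 32 models was 0.42, 0.73 and 0.98 RSI points. The largest is 0.98/3.1 = 32% of the target difference.

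**4. Continuous baseline RSI in the fixed model.** Let r be the correlation of baseline with 4-month RSI, with equal variances. Baseline then explains (1 − r)/2 of the variance of change. A median split of a normal baseline keeps 2/π = 0.637 of that share.

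- r = 0.3: explained share 0.35. Residual variance is 1 − 0.637 × 0.35 = 0.777 with the split and 0.650 with the continuous score. 0.650/0.777 = 0.837, a cut of about 16%.
- r = 0.7: explained share 0.15. Residual variance is 0.904 with the split and 0.850 with the continuous score. 0.850/0.904 = 0.940, a cut of about 6%.

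The correlation, the normal baseline and the median split are assumptions.

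**The case against.** The best defence is that ordinary covariate selection does little harm in a randomised trial. Baseline covariates are independent of allocation, so a rule that judges them by prognostic value leaves the treatment test near its nominal level. The simulation bears this out, and that part of the defence stands. A SAP is also promised before analysis, outcomes are analysed only at the end, and untransformed ANCOVA is the expected analysis. The SAP could close the gap completely. The article does not say that it will, and nothing in the text limits the analyst to a benign rule.

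A reader might infer more than the documents support:

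- **That the p-value and interval will be too optimistic.** This needs selection guided by the treatment estimate, which the article does not plan.
- **That the covariates are certain to be chosen from outcome data.** This is a natural reading of a model selection process, but no criterion is stated.
- **That site and severity may also be dropped.** The most literal reading allows it. In the first simulation the most favourable model then gave 10.6-23.6%, and 12.8-24.9% with a choice of log or rank analysis added. The natural reference of the sentence is the optional list just before it, so these figures are not relied on.
- **That selecting BMI or RFS would lose participants.** This assumes complete-case handling of covariates, which the article does not state.

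**Conclusion.** The point holds as a lack of guarantee. The article builds an undefined selection step into its single primary analysis and leaves a change of scale possible, so neither the 5% level nor an estimate in RSI points is secured by the text. Under selection that ignores the treatment estimate, inflation is negligible. If the model is picked by its treatment result, type I error reaches about 8-18% for assumed covariate shares of 5-40%. That range is a bound on what the wording permits and does not predict what the trial team will do. There is no separate figure for the scale switch alone; its main consequence is for what is being estimated. The sample size is unaffected. This should be fixed, because the remedy is nearly free now and much less credible after unblinding.

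**What to change.** Before unblinding, replace the selection step, in the SAP and in any protocol update, with one primary model: ANCOVA of change in RSI on treatment, site, severity group and continuous baseline RSI, on the original scale whatever the distribution. If residuals are skewed, keep that estimate and use robust or bootstrap intervals, naming in advance which of the two and what would trigger it, so that this does not become another open choice.

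Report one named extended model (adding gender, age, BMI, RFS and symptom categories) and any transformed or rank analysis as sensitivity analyses only. The secondary scores are to follow a similar strategy, so the same wording should cover them.

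The cost is a change of text. The trial was still recruiting at submission (201 of 332), and N does not change. What is given up is a possible gain in precision from the optional covariates, which is small if they are weakly prognostic. If the sponsor expects one of them to matter, it can be named in the fixed model now. Continuous baseline RSI is already collected and should give back some precision, about 6-16% of residual variance under the assumptions above.

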**Methods/design:**

A UK multi-centre, randomised, controlled trial for adults with persistent throat symptoms to compare the effectiveness of treatment with the proton pump inhibitor (PPI) lansoprazole versus placebo.

The trial includes a six-month internal pilot, during which three sites will recruit 30 participants in total, to assess the practicality of the trial and assess the study procedures and willingness of the patient population to participate. If the pilot is successful, three additional sites will be opened to recruitment, and a further 302 participants recruited across the six main trial sites. Further trial sites may be opened, as necessary. The main trial will continue for a further 18 months. Participants will be followed up for 12 months from randomisation, throughout which both primary and secondary outcome data will be collected. The primary outcome is change in Reflux Symptom Index (RSI) score, the ‘area standard’ for this type of assessment, after 16 weeks (four months) of treatment. Secondary outcomes are RSI changes at 12 months after randomisation, Quality of Life assessment at four and 12 months, laryngeal mucosal changes, assessments of compliance and side effects, and patient-reported satisfaction.

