### Objectives

The primary objective is to compare the symptomatic response in patients with persistent throat symptoms at the end of 4 months (16 weeks) of treatment with lansoprazole versus placebo.

Secondary objectives are as follows:To explore the feasibility of study recruitment by means of an internal pilot trial rehearsal whose data will be included in the main data for analysis.To compare the symptom response at the end of 4 months (16 weeks) of treatment with those at 12 months.To determine the utility of the Reflux Symptom Index (RSI) questionnaire, the Comprehensive Reflux Symptom Score (CReSS) questionnaire items and subscales, endolaryngeal examination findings as scored by the Reflux Finding Score (RFS) and patient demographics including age, gender, smoking and body mass index [18–20] as potential baseline determinants of treatment response. (Hence generating improved characterisation of the subgroup of suspected laryngopharyngeal reflux (LPR) patients most likely to benefit from acid suppression therapy.)To compare the patient-reported side effects and compliance with treatment and use of any other over-the-counter medication use in both arms.To compare changes in disease-specific quality of life—Laryngopharyngeal Reflux Health-related Quality of Life (LPR-HRQL)—in the two arms.

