Secondary outcomes are as follows:RSI changes as above, at 12 months after randomisation.Quality of life: change in LPR-HRQL total score and subscale at 4 and 12 months.Laryngeal mucosal changes—increased RFS—are widely prevalent in both normal volunteers (64–86 %) [31] and in throat symptom patients (38–51 %). The best predictor of EOR is pseudosulcus (67–90 % positive predictive value) [32, 33], but this is a rare finding. We propose to assess the RFS scored 0–29 by an independent observer, blind to treatment group as a response predictor, alongside patient characteristics (age, gender, smoking, body mass index) and the total, and the CReSS total and three subscales—oesophageal (14 items), upper airway (eight items) and pharyngeal (seven items).Estimates of compliance (pill count), side effects and current and/or planned use of over-the-counter medication.Patient-reported satisfaction.

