#### Data Monitoring and Ethics Committee

An independent DMEC will be convened to undertake independent review and will monitor efficacy and safety endpoints. The committee will consist of an independent chairperson, an independent clinician and an independent statistician, and will meet to discuss and advise on the inclusion of an interim analysis and possible adoption of a formal stopping rule for efficacy or safety. The committee will then meet at the end of the internal pilot and annually throughout the course of the trial.

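### A blanket rule against statistical analysis of safety data conflicts with the secondary objective of comparing side effects between arms, leaving only bare counts by arm if followed literally

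*Protocol article*

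**What the plan says.** Three places in the protocol article treat side effects as something the trial will compare or report as an outcome:

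- Objectives, among the secondary objectives: "To compare the patient-reported side effects and compliance with treatment and use of any other over-the-counter medication use in both arms".
- Outcomes, among the secondary outcomes: "Estimates of compliance (pill count), side effects and current and/or planned use of over-the-counter medication".
- Abstract, Methods/design, in the list of secondary outcomes: "laryngeal mucosal changes, assessments of compliance and side effects, and patient-reported satisfaction".

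The Statistical analysis section then says: "Safety data will not be subject to statistical analysis". No exception follows, and the article does not define safety data.

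The same section describes methods for other secondary outcomes: "The analysis of secondary outcomes will follow a broadly similar strategy when considering questionnaire scores or the change in questionnaire scores". It adds logistic regression for the proportion of participants whose follow-up RSI lies in the normal range. Neither method is directed at side effects.

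**The concern.** A stated objective and a stated analysis rule pull in opposite directions. If side effects count as safety data, which is the ordinary meaning, the rule removes any estimate of the difference between arms and any measure of its uncertainty. What remains is a count in each arm.

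This differs from an article that leaves the method for a secondary outcome to the analysis plan. Here the matter is settled, in the negative. An analysis plan that obeys the sentence can deliver the objective only as a tabulation. One that adds an estimate with an interval departs from the published protocol.

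What is at stake is how the harms results will read. The Background says that most controlled studies have not shown a significant benefit of PPI over placebo, so a small or null effect on symptoms is a realistic outcome, and readers will then look at side effects. Counts that happen to be similar are easily taken as evidence of no difference when the data may be compatible with an excess of several percentage points.

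**Working it through.** **Step 1: the passages side by side.**

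| Section | Content | Consequence |
|---|---|---|
| Objectives | Side effects to be compared in both arms | A between-arm contrast is intended |
| Outcomes; abstract | Side effects are a secondary outcome | They belong to the outcome data |
| Statistical analysis, on secondary outcomes | Methods for questionnaire scores and for RSI within the normal range | No method reaches side effects |
| Statistical analysis, on safety | No statistical analysis of safety data | The contrast is limited to description |

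The Statistical analysis section also says that outcome data will be analysed at the end of the study. Under the Outcomes section that includes side effects, so the section is in tension with itself unless safety data means something narrower. The article gives no narrower meaning.

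**Step 2: the sample size, which supplies the denominators.** The only calculated figure in the article is for the primary outcome. Inputs from the Sample size calculation section: standardised effect 0.4, "equivalent to a difference in change of RSI of 3.1 given a standard deviation of 7.7", and "90 % power and at the 0.05 significance level, allowing for 20 % loss to follow-up" (a two-sided test is assumed).

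- Normal approximation: n per arm = 2 × (1.96 + 1.2816)² / 0.4² = 131.3, so 132.
- Exact two-sample *t* test: 132.3, so 133 per arm, or 266 in total, as stated.
- Allowing for loss: 266 / 0.8 = 332.5, against 332 stated (166 per arm).

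The stated size reproduces to rounding. The point made here does not depend on it; it only gives 133 (completing) and 166 (randomised) per arm as plausible denominators for side effects.

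**Step 3: what an interval would show (illustration).** The article gives no side-effect rates, so p below is assumed, with the same rate in both arms. The 95% half-width for the risk difference is 1.96 × √(2p(1 − p)/n).

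| Assumed rate p | n = 133 per arm | n = 166 per arm |
|---|---|---|
| 5% | 5.2 points | 4.7 points |
| 10% | 7.2 points | 6.5 points |
| 20% | 9.6 points | 8.6 points |
| 30% | 11.0 points | 9.9 points |
| 40% | 11.8 points | 10.5 points |

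Two entries in full: at p = 0.20 and n = 166, 1.96 × √(0.32/166) = 1.96 × 0.0439 = 0.086; at p = 0.10 and n = 133, 1.96 × √(0.18/133) = 1.96 × 0.0368 = 0.072.

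So if about 20% in each arm of 166 reported a side effect, the observed difference would be zero with a 95% interval of roughly −8.6 to +8.6 points. Two equal counts do not convey that.

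**The case against.** The strongest reply is that no contradiction is proven. Comparing need not mean testing or modelling: a table of side effects by randomised arm is a comparison, and the Statistical analysis section does not forbid it. This stands. A reader might infer that the objective is left unanswerable; the document does not support that, because descriptive reporting by arm remains open.

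A second reply is that safety data may mean only adverse events, serious adverse events and suspected unexpected serious adverse reactions, which the section on withdrawal of participants names, while patient-reported side effects stay among the outcome data. Or the authors may have meant only that no hypothesis tests would be done. Either is possible, but the article says neither, and nothing in it draws that line. The reply shows how the sentence might be repaired; it does not show that the sentence is sound as written.

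A third reply concerns the numbers. The rates are assumed, and the half-widths describe how precisely this trial can measure harms. They do not measure an error caused by the sentence. This is correct, and they are offered only on that footing. An observed excess of 5 to 8 points at a 20% rate would in any case have an interval that includes zero; the interval's value is in showing that imprecision.

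A fourth reply is that the article's aim is effectiveness and that it does not present itself as a weighing of benefit against harm. That is fair, and limits how much weight the point can bear. The side-effect comparison is nevertheless one of the article's own objectives.

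A reader might also see a conflict with the Data Monitoring and Ethics Committee, which "will monitor efficacy and safety endpoints". There is none: the committee's work is oversight while the trial runs, including advice on a possible stopping rule. It neither contradicts nor replaces the comparison at the end of the trial.

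**Conclusion.** The point holds as a conflict in the text. The article sets a between-arm comparison of side effects as an objective, lists side effects as an outcome, and then excludes safety data from statistical analysis without separating the two. Read literally, the comparison would consist of counts by arm with no difference and no interval.

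It is worth correcting but limited in reach. The primary analysis and the sample size are untouched, and no figure needs correcting. The illustrative precision, about ±6.5 to ±9.6 percentage points, rests on assumed rates of 10% to 20%, equal in both arms, with 133 to 166 participants per arm; across 5% to 40% the range is about ±5 to ±12 points. The conclusion that the passages need reconciling does not depend on these assumptions.

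**What to change.** Replace the sentence in the Statistical analysis section with a statement along these lines: side effects and serious adverse events will be summarised by arm as the number and proportion of participants with at least one event, with the between-arm risk difference and its 95% confidence interval, and without formal hypothesis tests. This respects any wish to avoid underpowered testing of harms and still gives the objective an estimate with stated uncertainty.

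The cost is a sentence in the protocol and one extra table from data already collected. The intervals will be wide and should be reported as such. The article says that the full analysis plan will be written before analysis starts, so the change can be carried into it.
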